# Prospective observational study investigating the factors impacting the safety of endoscopic right-sided colectomy for colon cancer in Japan (SCaRLET study): a study protocol

**DOI:** 10.1186/s12893-025-03362-1

**Published:** 2025-11-29

**Keywords:** Colorectal cancer surgery, Laparoscopic colorectal surgery, Complications, Robotic surgery, Vascular injury

## Abstract

**Background:**

Right-sided colon resection is generally regarded as a relatively safe laparoscopic procedure with a low complication rate. Paradoxically, right hemicolectomy has been reported to carry a fourfold higher mortality rate compared to low anterior resection for rectal cancer in Japanese real-world data, despite the latter being more technically demanding and associated with a higher complication rate. This study aims to investigate the factors that influence the safety of laparoscopic right-sided colon resection.

**Methods:**

Patients undergoing laparoscopic or robot-assisted surgery for right-sided colon cancer at participating institutions in the Laparoscopic Colorectal Resection Study Group will be prospectively enrolled between 3 July 2024 and 31 May 2026. This multicenter study expects to enroll a total of 2,000 colorectal cancer cases from 73 facilities nationwide. The primary endpoint is the incidence of postoperative complications classified as Clavien–Dindo grade ≥ III. Risk factors contributing to these severe complications will be analysed. As a key secondary endpoint, the incidence and predictors of intraoperative vascular injury near the superior mesenteric vein will also be evaluated.

**Discussion:**

This nationwide, multicentre, prospective study (SCaRLET study) will provide critical insights into the safety of laparoscopic and robot-assisted right-sided colectomy. By evaluating 2,000 cases under standardised conditions, the study aims to clarify the actual incidence and causes of severe postoperative complications and intraoperative vascular injuries, which remain poorly understood despite the procedure’s perceived safety. Comprehensive data collection and adherence to routine clinical practice will support accurate risk assessment and enhance the generalizability of findings. The results are expected to inform best practices and contribute to improving surgical safety in colorectal procedures including indication of colectomy both in Japan and internationally.

**Trial registration:**

This study was registered in the Japan Registry of Clinical Trials on 3 July 2024 (jRCT1010240021).

**Supplementary Information:**

The online version contains supplementary material available at 10.1186/s12893-025-03362-1.

## Background

Laparoscopic surgery for colorectal cancer is becoming more common worldwide and has demonstrated superiority to open surgery regarding short-term outcomes [1–3] and non-inferiority regarding long-term outcomes [4–6]. Among laparoscopic colorectal resections, right-sided colectomy is a relatively safe procedure, with few complications. An annual report of a Japanese nationwide survey in 2020 indicated that right hemicolectomy had a lower complication rate (8.0%) compared to low anterior rectal resection (11.1%) [7]. However, right hemicolectomy had a high 30-day mortality rate of 1.4%, four times more than that of low anterior rectal resection, which is a more difficult procedure with a higher complication rate [7]. More than 30% of patients undergoing right hemicolectomy are older than 80 years, which is more than twice as many as those undergoing low anterior rectal resection [8]. This older population might include many high-risk patients, and surgery might be indicated regardless. One hypothesis is that postoperative mortality following right hemicolectomy is primarily influenced by non-operative factors such as advanced age and frailty. However, operative factors — including intraoperative complications and delayed recognition of clinical deterioration — may also play a role. In other words, a single complication may present more severely, with a delayed response exacerbating severity. Therefore, further scientific investigation is required to clarify the factors affecting severe complications, including mortality, after laparoscopic right-sided colectomy.

Regarding procedural issues, intraoperative vascular injury remains a major complication of this technique. Injury to the superior mesenteric vein (SMV) and surrounding vasculature can cause major bleeding and subsequent massive bowel resection. Approximately 3% of D3 dissections result in vascular injury [8]. Moreover, minor injuries that do not result in major bleeding may be encountered clinically; however, they do not significantly affect final outcomes. Nevertheless, clinicians, particularly young surgeons, should be aware of these risks to safely perform the procedure. Clarifying the frequency and risk factors of intraoperative vascular injuries is crucial. Therefore, we designed the current prospective observational study to investigate factors affecting the intraoperative vascular injury rate as additional safety indicators.

Moreover, several concerns regarding right-sided colectomies require resolution. First, right-sided colectomy involves complete mesenteric excision (CME; in which regional lymph nodes in the mesentery are completely removed) and central vascular ligation (CVL; in which the dominant vessels in the mesentery at the trunk are removed) [9]. CME with CVL is technically feasible [8, 10, 11] and oncologically beneficial [12–14]. However, the interpretation of the ‘trunk’ is controversial in Japan [15]. It remains inconclusive whether the left margin of the anterior aspect of the SMV (D3v) or the superior mesenteric artery (SMA) (D3a) is appropriate (technical safety and oncological benefit) for the most central margin of lymph node dissection, along with CVL. Second, it remains unclear which surgical technique is the safest among the medial approach [16–18], the cranial approach [19], and approaches preceded by retroperitoneal dissection [20, 21]. A survey conducted by the Japan Society of Laparoscopic Colorectal Surgery (JSLCS) demonstrated that the medial and retroperitoneal approaches were the two main approaches (Figs. 1 and 2). However, few reports confirm which is the safest procedure [22–24]. Moreover, outcome superiority between robotic and laparoscopic surgery for right hemicolectomy remains inconclusive [25–28]. Third, the surgeon’s proficiency may play an important role in safety. The participation of surgeons certified through the Endoscopic Surgical Skill Qualification System, as defined by the Japanese Society for Endoscopic Surgery, has been shown to contribute to ensuring surgical safety in rectal cancer procedures [29, 30]; however, this has not been clarified in laparoscopic right-sided colectomy. Moreover, the safest surgical technique (medial or retroperitoneal approach, robotic or not) to be performed by young surgeons (e.g., before being qualified as a board-certified gastrointestinal surgeon) remains to be determined. Finally, the safest anastomotic method remains unclear (Fig. 3), with the most significant issue being whether intracorporeal or extracorporeal anastomosis is more useful [31–34]. In the current study, we structured the data collection to address these unresolved issues through a large-scale prospective cohort.

**Fig. 1 Fig1:**
[figure not shown]
Questionnaire regarding the preferred approach for conventional laparoscopic right colectomy**.** A nationwide questionnaire was conducted in 2023 by the Japan Society of Laparoscopic Colorectal Surgery. The most preferred approach in each institution is shown. According to the survey, the medial and retroperitoneal approaches are the most preferred

**Fig. 2 Fig2:**
[figure not shown]
Questionnaire regarding the preferred approach for robot-assisted right colectomy. A nationwide questionnaire was conducted in 2023 by the Japan Society of Laparoscopic Colorectal Surgery. The most preferred approach in each institution is shown. According to the survey, the medial and retroperitoneal approaches are the most preferred

**Fig. 3 Fig3:**
[figure not shown]
Questionnaire regarding the preferred anastomosis for laparoscopic right colectomy. A nationwide questionnaire conducted in 2023 by the Japan Society of Laparoscopic Colorectal Surgery revealed institutional preferences for anastomosis techniques. (**a**) Extracorporeal anastomosis was predominant in conventional laparoscopic surgery, (**b**) while intracorporeal anastomosis was favoured in robot-assisted procedures

Given the above background, we have designed this prospective observational study to investigate factors influencing the safety of laparoscopic right-sided colon resection.

## Methods

### Eligibility criteria

Patients scheduled to undergo laparoscopic surgery for right-sided colon cancer between 3 July 2024 and 31 May 2026 at a facility affiliated with the JSLCS will be eligible for this study.

### Selection criteria

Cases with a diagnosis of adenocarcinoma.Cases in which laparoscopic ileocecal resection, laparoscopic right hemicolectomy, or laparoscopic extended right hemicolectomy with D2 or D3 dissection are planned for clinical stage 0, I, II, or III colon cancer in the caecum, ascending, or transverse colon.Robot-assisted surgical cases will be eligible for inclusion only after the participating institution has demonstrated procedural proficiency through completion of at least 10 prior cases of ileocecal resection, right hemicolectomy, or extended right hemicolectomy for right-sided colon cancer.

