### Endpoints

The primary endpoint is the incidence of postoperative complications (Clavien–Dindo classification grade ≥ III) [35]. The rate of severe postoperative complications in all eligible patients will be investigated, and risk factors affecting them will be determined.

A key secondary endpoint is the incidence of intraoperative vascular injury around the SMV. The rate of intraoperative vascular injury around the surgical trunk in all eligible patients will be investigated, and risk factors affecting it will be extracted.

Other secondary endpoints include the incidence of postoperative complications (Clavien–Dindo classification grade ≥ II), 5-year overall survival, recurrence-free survival, and other short- and long-term outcomes (operative time, blood loss, conversion rate, degree of lymph node dissection, intraoperative complication rate, reoperation rate, R0 resection rate, local recurrence rate in the whole cohort and by stage, and incidence of bowel obstruction and herniated abdominal wall scarring). Factors influencing the above endpoints will be determined for all eligible patients. Furthermore, comparisons will be made between each subgroup, as shown in Table 1.

**Table 1 Tab1:** Secondary endpoints

1. Short-term results by approach (a. Medial approach vs. retroperitoneal approach; b. Medial approach vs. cranial approach; c. Retroperitoneal approach vs. cranial approach; a–c for laparoscopic surgery and robotic surgery, respectively)
2. Short-term results of robot-assisted and laparoscopic surgery (Comparison in all approaches, medial approach, retroperitoneal approach, and in each ASA-PS, respectively)
3. Short-term results by degree of lymph node dissection (D2, D3v, D3a)
4. Long-term results by approach, robot or laparoscopy, and degree of dissection
5. Impact of experience on short-term and long-term outcomes after the surgery performed by the surgeons before obtaining board certification in gastrointestinal surgery (including the investigation by each approach, robot/laparoscopy, and degree of lymph node dissection)
6. Impact of surgeons’ case volume prior to obtaining board certification in gastrointestinal surgery on short- and long-term outcomes following robot-assisted procedures
7. Impact of the participation of Endoscopic Surgical Skill Qualification-certified surgeons in surgery and their role in the procedure on short- and long-term outcomes
8. Impact of anastomosis method on short- and long-term outcomes

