Participating institution backgroundInstitution type and sizePatient backgroundPatient age; sex; body mass index; American Society of Anesthesiologists Physical Status; Eastern Cooperative Oncology Group performance status; albumin level; lymphocyte count; presence of dementia, diabetes, chronic kidney disease, chronic liver disease, or respiratory comorbidities; history of cardiac or cerebrovascular disease; use of steroids/immunomodulators and antithrombotic drugs; preoperative bowel obstruction; preoperative anaemia; abscess or peritonitis; preoperative therapy; history of laparotomy; timing of surgery; primary tumour location; and tumour stage at initial diagnosis (clinical stage, T factor, N factor).Technique and surgeonsWhether the surgeon is a board-certified gastrointestinal surgeon, whether an Endoscopic Surgical Skill Qualification-certified surgeon participates in the operation and his or her role, the approach, blood vessels to be dissected, procedure of dissecting the accessory right colic vein (via the cranial or caudal side), level and direction of lymph node dissection, instruments used during node dissection, method of anastomosis, combined resection of other organs, whether a robot is used, number of previous robotic-assisted right-sided colon resections (ileal resection, right hemicolectomy, or extended right hemicolectomy), and whether a robotic surgery proctor participates in the surgery if robotic surgery is used.Surgical outcomesThe date of surgery, operation time, blood loss, presence of intraoperative vascular injury, other intraoperative complications, 30-day postoperative survival, open conversion, intraoperative blood transfusion, details and grade of postoperative complications within 30 days (Clavien–Dindo classification grade ≥ II), onset and date of intervention for cases with anastomotic leakage/deep wound infection (surgical site infection [SSI]), enforcement and date of reoperation, drain placement, anti-adhesive placement, date of discharge, and operative death.In cases of intraoperative vascular injury:Timing of intraoperative vascular injury; response to intraoperative vascular injury; unplanned bowel resection due to bleeding; open conversion due to bleeding; final post-haemostatic status; and amount of blood transfusion, blood products, and albumin administered from intraoperative to postoperative day 3.Surgical deathsCause of death, date of death, and date of therapeutic intervention.Pathological and histological findings and postoperative courseTumour diameter, histological type (main), pathological stage, T-factor, N-factor, R-status, number of harvested lymph nodes, number of lymph node metastases, presence and details of adjuvant therapy, survival outcome, date of confirmation of final survival outcome, date of confirmation of recurrence, and type of initial recurrence.Patients with pStage 0 and pStage IV will be censored, and no follow-up will be performed after initial postoperative discharge. The development of intestinal obstruction (Clavien–Dindo classification grade ≥ II) and abdominal wall scar hernia will be investigated during follow-up. Patients will be followed up during the postoperative period according to the Japanese Society for Cancer of the Colon and Rectum guideline schedule, and tumour marker levels, thoracoabdominal computed tomography (CT) results, and colonoscopy results will be collected. Omitting observations as part of routine medical care will be deemed acceptable at the discretion of the treating physician [36].

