Secondary endpoints: Summary statistics for patient background and other surgical outcomes will be calculated. A multivariate logistic regression or multiple regression analysis will be performed using the factors listed in the survey items that may influence outcomes. A random-effects model will be used to account for differences between the centres. The main endpoint for short-term outcomes for each subgroup is postoperative complications (Clavien–Dindo classification grade ≥ II), and group comparisons will be conducted after propensity score matching (differences between groups will be tested using Student’s t-test and the χ^2^ test) and logistic regression to identify confounders. Multiple regression analysis will be used to analyse continuous variables. A random-effects model will be used to account for the differences between institutions. The Kaplan–Meier method will be used to plot cumulative late complication curves, local and overall recurrence-free survival curves, and overall survival curves for long-term outcomes. To account for confounding factors, a multivariate Cox regression analysis will be performed using preoperative and postoperative factors that may contribute to recurrence and late complications, and risk factors will be examined. In addition to regression analysis of factors, each factor will be discussed from clinical and medical perspectives to reach a combined perspective.

The number of experienced cases will be added to the factors in the multivariate analysis to examine their effect on the outcome. The correlation of the number of cases experienced and outcomes (operation time and blood loss) with the learning curve will be evaluated using the moving average method and the cumulative sum curve.

Statistical significance will be set at *p* < 0.05.

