## Discussion

Successfully performing surgical procedures without intra- or postoperative complications is critical. A national survey in Japan demonstrated that the mortality rate of right hemicolectomy was higher than that of low anterior resection [7]. However, no detailed studies regarding the factors influencing the safety of this procedure have been conducted. Therefore, we will conduct the SCaRLET study to identify the rate and cause of severe perioperative complications in laparoscopic right-sided colectomy.

To the best of our knowledge, this will be the first large prospective study of laparoscopic right-sided colectomy in Japan, with nearly equal numbers of laparoscopic and robotic procedures. This study is characterised by a low event selection bias owing to its prospective nature. It will be conducted at Japanese institutions that excel in JSLCS, with high proficiency levels of performing laparoscopic and robotic surgeries. Hence, the institutional experience will not affect the study outcomes, potentially determining the actual safety of the procedure. We will investigate the actual incidence and causes of high mortality rates due to the procedure, which have not yet been clarified. Furthermore, we will investigate the actual incidence and causes of intraoperative vascular injury, which may be the only critical aspect in D3 lymph node dissection.

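### The 10-case institutional floor covers robot-assisted cases only and does not say whether the prior cases must be robotic; if they must, the robot versus laparoscopy comparisons may be confounded by institution

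*Protocol article*

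**What the plan says.** All points are in the protocol article.

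- **Entry of robotic cases (Selection criteria).** "Robot-assisted surgical cases will be eligible for inclusion only after the participating institution has demonstrated procedural proficiency through completion of at least 10 prior cases". The full description of the qualifying cases is "at least 10 prior cases of ileocecal resection, right hemicolectomy, or extended right hemicolectomy for right-sided colon cancer".
- **Entry of laparoscopic cases (Eligibility criteria).** Patients having surgery "at a facility affiliated with the JSLCS will be eligible for this study". Neither this section nor Selection criteria sets a minimum number of earlier laparoscopic cases.
- **Comparison (Endpoints, Table 1).** Item 2 is "Short-term results of robot-assisted and laparoscopic surgery (Comparison in all approaches, medial approach, retroperitoneal approach, and in each ASA-PS, respectively". Item 4 extends the platform comparison to long-term results.
- **Analysis (Statistical analysis).** "The main endpoint for short-term outcomes for each subgroup is postoperative complications (Clavien–Dindo classification grade ≥ II". Groups are compared after propensity score matching and by logistic regression. A random-effects model handles differences between institutions, and the number of experienced cases enters the multivariate models.
- **Data collected.** Observation, investigation data, and methods lists the "number of previous robotic-assisted right-sided colon resections" and gives no laparoscopic counterpart. Definition of assessment data records institution type, and an annual volume that pools laparoscopic and robotic resections.
- **Discussion.** After describing the sites as highly proficient in both techniques, it concludes: "Hence, the institutional experience will not affect the study outcomes".

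**The concern.** The rule conditions entry on institutional history for one arm of a planned comparison and not for the other. Two consequences follow if the 10 cases must be robotic. First, a site that has not qualified appears in the laparoscopic group only, so platform and institution are linked through eligibility. Second, the first robotic cases at each site are missing, so the robotic results and the learning-curve analysis begin after start-up.

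The wording also leaves open which cases count. Two sites could apply the same sentence differently, and the robotic cohort would then not be defined in one way across the 73 facilities.

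At stake is the reading of the platform comparison. The Background calls this question inconclusive and says that data collection was structured to address it.

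**Working it through.** The documents give no figure for this effect, so there is none to reproduce. The target of 2,000 serves the precision of the overall complication rate and does not bear on this point.

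**1. Which prior cases count?** The criterion names three resections and no platform. The data-collection section does name the platform when it asks for a robotic count. A floor on robotic cases, described as showing proficiency, suggests that robotic cases were meant. The words do not say so.

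**2. If any right-sided resection counts.** Expected recruitment is 2,000 / 73 = 27.4 cases per site. Over about 23 months that is 27.4 / (23/12) = 14.3 per site-year. At that average rate, 10 cases take 10 / 14.3 = 0.7 years, so few sites would be expected to fall short. The rule then screens very little and the asymmetry largely disappears.

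**3. If only robotic cases count.** Let *s* be the share of laparoscopic cases from sites or periods that do not qualify, and RR the risk there relative to qualified sites. Assume no true platform effect and a risk of 5% at qualified sites (the rate used under Target number of cases, for grade ≥ III; no grade ≥ II rate is given).

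- Laparoscopic risk: p = 0.05 × [(1 − s) + s × RR]
- Spurious odds ratio, robot to laparoscopy: OR = (0.05/0.95) / [p/(1 − p)]
- Chance of p < 0.05 in the robot's favour: Φ(|p − 0.05|/SE − 1.96), with SE² = [0.05 × 0.95 + p(1 − p)]/1,000. The Discussion expects nearly equal numbers of the two procedures, hence 1,000 per group.

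| s | RR | p | OR | Chance |
|---|---|---|---|---|
| 0 | any | 5.00% | 1.00 | no bias |
| 10% | 1.5 | 5.25% | 0.95 | 4% |
| 25% | 1.5 | 5.63% | 0.88 | 9% |
| 25% | 2 | 6.25% | 0.79 | 23% |
| 50% | 2 | 7.50% | 0.65 | 64% |

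With no bias the last column would be 2.5%. The base risk matters little: at 8.0%, the survey complication rate in the Background, s = 25% and RR = 1.5 give 8.0% × 1.125 = 9.0% and OR = (0.08/0.92)/(0.09/0.91) = 0.88. The sign depends on RR. With RR = 1/1.5 and s = 25%, p = 0.05 × (0.75 + 0.167) = 4.58% and OR = 1.10, against the robot.

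For scale, s = 25% of 1,000 is 250 cases, or 250 / 27.4 = about 9 average-sized sites. s = 50% is about 18 sites.

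Both *s* and RR are assumptions; no passage gives either. The table ignores all adjustment.

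**4. Would the stated adjustments remove it?** A random intercept treats the site effect as unrelated to platform, which is doubtful when some sites can supply one platform only. At 5% there are about 27.4 × 0.05 = 1.4 events per site, so site intercepts would be shrunk heavily and would correct little. An experience count listed only for robotic resections cannot be balanced between the groups, and pooled annual volume does not identify robotic qualification. None of these brings back the excluded early robotic cases.

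**5. The Discussion statement against the rest.** Selection criteria gates on institutional experience. The data sections record institution type and volume. Statistical analysis models institutions and adds the number of experienced cases. A plan that does all this cannot also take it as given that institutional experience has no effect.

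**The case against.** The strongest reply is that a start-up exclusion is a legitimate design choice. Leaving out the first cases of a new technique can be seen as avoiding a bias against it, and a site with fewer than 10 robotic cases is not thereby worse at laparoscopy. All sites belong to one society and are described as proficient in both techniques, and Table 1 items 5 and 6 still study surgeons before board certification. The article does not list its matching variables; those are commonly left to the full protocol or analysis plan, so their absence is no fault.

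Most of this stands, and it limits the point. A reader might infer that the rule favours the robot. The documents do not support that: no passage shows a higher laparoscopic risk at non-qualifying sites, and the sign reverses with RR. A reader might also infer that screened institutions are set against unscreened ones. That is not so either, because qualified sites can supply both techniques. Nor can the ambiguity and the bias both apply in full: the bias needs the robotic reading.

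What the reply does not answer is the undefined count, the one-platform sites under the robotic reading, and the Discussion statement.

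**Conclusion.** The point holds in limited form. The floor applies to robot-assisted cases only, and its qualifying cases are not defined by platform. On the robotic reading, Table 1 items 2 and 4 may be confounded by institution, and they describe robotic surgery after site start-up; the stated adjustments do not reliably remove this. On the any-resection reading, little asymmetry remains.

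Neither direction nor size can be determined from the documents. The odds ratios above rest wholly on assumed values of *s* and RR, and the larger ones need a quarter to a half of laparoscopic cases to come from non-qualifying sites at doubled risk. The Discussion statement is unsupported on either reading. The consequences are confined to secondary, observational comparisons.

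**What to change.** 1. **Selection criteria.** Establish how sites have applied the rule since enrolment opened in July 2024, reconcile the wording with that practice, and state which prior cases count. If practice differed between sites, report it.
2. **Table 1 items 2 and 4.** Add a robot versus laparoscopy comparison limited to institutions that had met the criterion by the date of surgery, or to institutions contributing both techniques. Report it beside the all-institution comparison.
3. **Discussion.** Delete or replace the statement that institutional experience will not affect outcomes, and describe the robotic and learning-curve results as conditional on a qualified institution.

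The cost is low. The both-techniques version needs only the institution and the robot-use field already recorded. The date-based version needs one item per institution that the article does not list: a simple yes for sites qualified before enrolment began, and a date for those that qualified later. Some laparoscopic cases drop out of the added comparison, which loses a little precision there. The restriction deals with confounding by institution but cannot recover the early robotic cases, so the limit on scope must still be stated.
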